### Process evaluation

Embedded within THRIVE is a realist process evaluation which will carefully monitor what is happening within the trial. Realistic evaluation [54] will provide the theoretical rationale for the process evaluation, which will seek to answer the following questions:
How faithfully are ETPB and MB implemented?What are the mechanisms by which they work, if they do, who do they work for and how?What contextual factors are necessary for the programmes to function, or might prevent them from functioning?

The mixed-methods design will include:
Pre-training and post-training/intervention questionnaires for practitioners and mothers to be and post-session evaluation forms.Participant observation of practitioner training and the delivery of a series of antenatal sessions.Semi-structured interviews with practitioners, mothers to be, partners and referring practitioners.Telephone interviews with mothers examining the content of the postnatal components of ETPB and MB.

The findings will aid interpretation of the outcomes of THRIVE by providing a greater understanding of how the interventions work (if they do), the extent and quality of their implementation, contextual factors facilitating and constraining intervention functioning, variations in response within and between subgroups of vulnerable parents and benefits or unintended consequences of either intervention. For further information, please consult [55].

A timeline of activities for participants in each arm of the trial is shown in Fig. 1 and a schedule of study activities is shown in a SPIRIT diagram (Fig. 2). A Standard protocol items: recommendation for interventional trials (SPIRIT) checklist indicating where standard protocol items for randomised controlled trials are located within this protocol is included in Additional file 4.

**Fig. 1 Fig1:**
[figure not shown]
Timeline of participant activities. HADS+1, Hospital Anxiety and Depression Scale enhanced by the outwardly-directed irritability questions adopted from the Adult Wellbeing Scale; EQ-5D, EuroQol 5 Dimensions - a standardised instrument used as a generic measure of health; SNiPs, Special needs in pregnancy; CAU, care as usual; ETPB, Enhanced Triple P for Baby; MB, Mellow Bumps

**Fig. 2 Fig2:**
[figure not shown]
Standard protocol items: recommendation for interventional trials (SPIRIT) diagram indicating the schedule of THRIVE study activities. GP, General Practitioner; EQ-5D-3L, EuroQol 5 Dimensions, 3 Levels - a standardised instrument used as a generic measure of health; CAU, care as usual; ETPB, Enhanced Triple P for Baby; MB, Mellow Bumps; NHS, National Health Service; A&E, Accident and Emergency

### Planned longer-term follow up using routine data (still to be funded)

Longer-term outcomes will be assessed by linking the short-term outcomes identified in the study to longer-term impacts on health and wellbeing for both mother and child via factors identified from the literature. This trial aspect will rely on linking published associative data and any short-term primary outcomes identified in the trial with long-term costs and benefits in health and education, and other effects such as the effect on employment. Routine data, such as the Strengths and Difficulties Questionnaire, [56] collected by health and social care professionals when the child is around 30 months old, will facilitate the measurement of longer-term outcomes including social and emotional wellbeing, language development, educational attainment, incidences of maltreatment or neglect and placement of children onto the “risk register”/into child protection services. Future linkage will also assess the costs of health, social care and broader education and employment impacts. In addition, it will provide important information in terms of health status and the use of services across the study groups.

All data linkage will be initiated by the Robertson Centre for Biostatistics, which is a registered Clinical Trials Unit (CTU), using the NHS GGC’s Safe Haven that has been developed to support secondary research use of clinical data. Data from NHS A&A will also be required and access to these data via Safe Haven should become available during the life of THRIVE. If this does not occur, then the research team will seek permission from the NHS Information Services Division (ISD Scotland) to link NHS records for NHS A&A’s patients into the Safe Haven.

The research team understands that data linkage at the individual level is sensitive and raises issues of privacy, and will ensure that all data linkage undertaken adheres to the standards outlined by ISD Scotland [57]. In addition, the NHS GGC’s Safe Haven is subject to a local privacy advisory committee that will ensure that that risks to privacy at the individual patient level are minimised.

### Randomisation

Participants will be allocated a unique identification (ID) number by the research team on entry to the study. This ID number will be used to anonymise completed baseline questionnaires, which will be delivered to the CTU for data entry. The CTU will block-randomise participants to the three trial arms using a computer-generated sequence, stratified by parity (number of children), severity of psychiatric symptoms (measured by the BSI, 53) and history of substance dependency, which will be determined based on baseline questionnaire responses. For every 12 participants randomised, two will receive CAU, five will be offered ETPB and five will be offered MB. The research team will receive details of each participant’s intervention arm allocation by email from the CTU based on their ID number. The research team will then contact the participant to let them know which trial arm they have been allocated and to provide details of the group session for those allocated to ETPB or MB. Where consent is provided, the research team will also send a letter to the participant’s health and social care providers to let them know the intervention arm allocation.

### Blinding

Researchers at the MRC/CSO SPHSU, University of Glasgow (UoG) and at Glasgow Caledonian University (GCU) will not be blinded to trial arm allocation due to their direct contact with participants. CTU statisticians and data processers will only receive anonymised data and will not have direct contact with participants. Researchers at UoM will be blinded to trial arm allocation, providing a single-blind evaluation of the quality of mother-infant interactions.

### Storage and anonymisation of confidential data

All data collected will be stored securely, in accordance with the UoG Best Research Practice Guidelines, and managed in accordance with the Data Protection Act 1998 and the General Data Protection Regulation (from May 2018), in either locked filing cabinets or password-protected databases. Data will be accessible only by members of the UoG research team and their research partners at GCU, UoM and the Universities of Aberdeen and Newcastle. All of the data collected will be kept separate from any individual participant identifiers and secure. Participants will be given their own unique ID number in order to link their data throughout the trial. All quantitative data collected as part of the study will be securely transferred to the Robertson Centre for Biostatistics CTU for data entry and cleaning.

Qualitative interview data and recordings of intervention delivery sessions will be transcribed by an external (security checked) transcription agency, and securely stored by researchers based at the UoG and GCU. Video-recordings of mother-infant interactions will be transferred to the UoM using a secure Internet platform designed and maintained by the Robertson Centre for Biostatistics for observer-rated coding using the CARE Index and the MPOS. The one exception to this rule is to allow the secure transfer of a small number of anonymous video-recordings to Mellow Parenting for rater quality-control checks.

In all cases data sharing and confidentiality agreements will be line with the UoG regulations. Permission will be sought from participants for archiving purposes during trial consent, and the trial consent form will notify participants that their data and their child’s data will be made available to the funders in anonymised form.

### Statistical analysis

THRIVE has been powered based on the primary outcome measure of maternal mental wellbeing. The efficacy of ETPB and MB will be analysed at a significance level of 2.5% in order to maintain an overall type I error rate of 5%. Two analyses, performed in a hierarchical fashion so that no further *p* value adjustment is necessary, will be undertaken. In analysis 1, the combined intervention groups (ETPB and MB) will be compared with CAU. If analysis 1 detects a difference at a 2.5% level of statistical significance, analysis 2 will compare ETPB with MB as a primary analysis, to be judged at a 2.5% statistical significance level. If analysis 1 does not yield a statistically significant result, then analysis 2 will be considered a secondary analysis.

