Sensitive mother-infant interactions are characterised by reciprocal communication from an early stage, which facilitates language but also significantly reduces the risks of maltreatment. This is thought to be due to mothers perceiving their infants as co-operating with them [11]. Mother-infant interactions that succeed in facilitating secure future attachments enable overall development, including language, and may set infants onto a more positive life trajectory. The evidence for the effect of early child development on health and wellbeing in later life is widely accepted and early childhood interventions, such as the High/Scope Perry Preschool Project [12], the USA Family Nurse Partnership (FNP) [13], the Carolina Abecedarian Project [14] and the Chicago Child-Parent Programme [15], have had positive effects on a number of child development domains and on wellbeing and life success in adulthood. Furthermore, early intervention, is generally more cost-effective than intervening later, and is most effective in the antenatal period [16]. However, many applied economic evaluations in the area of home visiting and parenting have had diverse economic objectives and methodological problems including the lack of a societal perspective and limited cost analysis.

We hypothesise that the provision of a parenting support intervention, *Enhanced Triple P for Baby* (ETPB) or *Mellow Bumps* (MB), in addition to routinely provided care during the antenatal and early postnatal phase, will be a cost-effective way of improving maternal mental health, increasing the dyadic synchronicity and sensitivity of mother-infant interactions, reducing the risk of child maltreatment and improving child language and socio-emotional development. The Trial of healthy relationship initiatives for the very early years (THRIVE) is a three-arm, randomised controlled trial of women with additional health and social care needs in pregnancy aiming to compare ETPB plus care-as-usual (CAU) or MB plus CAU with CAU. Based on recent economic evaluation research carried out on a similar trial in Oxfordshire [17, 18], THRIVE will include a comprehensive economic evaluation.

The primary research questions that will be addressed by THRIVE are:

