Do participants receiving ETPB plus CAU or MB plus CAU have significantly lower anxiety, depression and outwardly directed irritability compared with those receiving CAU alone when their infants are around 6 months old?Do participants who receive ETPB plus CAU or MB plus CAU have more sensitive interactions with their infants compared with those receiving CAU alone when their infants are around 6 months old?

The secondary research questions that will be addressed by THRIVE are:
Do infants whose parent(s) receive ETPB plus CAU or MB plus CAU show more cooperative behaviour signs than those whose parent(s) received CAU alone?Do ETPB or MB lead to changes in the number of children flagged as “at risk” on the social services risk register, under a child protection plan, taken into local authority care or attending an accident and emergency department?Do ETPB or MB lead to improvements in the socio-emotional development of children around 30 months old?Do ETPB or MB lead to an improvement in language development in children around 30 months old?Do ETPB or MB lead to an improvement in longer-term educational and health outcomes for children?Is either ETPB or MB cost-effective for the National Health Service (NHS) or society more broadly, in the long term?Do differences in programme fidelity, practitioners’ characteristics and motivation, mothers’ engagement, the intervention mechanisms and contextual factors affect mother and infant outcomes?Does fathers’ involvement or support affect mothers’ engagement with ETPB or MB?How do participants’ experiences of being parented influence their own parenting values and behaviour?

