#### Power calculation

In order to have 90% power to detect an effect size of 0.4 for Analysis 2 (ETPB versus MB) 157 participants are required in both the ETPB plus CAU and MB plus CAU groups. Comparing these 314 participants with CAU alone in analysis 1 (ETPB and MB vs CAU), requires 61 participants in the CAU alone group to achieve 90% power. Therefore, 375 participants are required in a ratio of ETPB:MB:CAU of approximately 5:5:2. To allow for 25% attrition at follow up, 500 participants will be recruited and randomised.

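### The confirmatory hierarchy never compares ETPB alone or MB alone with CAU; both contrasts can be added behind Analysis 1 without raising the error rate, but with limited power

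*Protocol article*

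**What the plan says.** The Background section describes a trial "aiming to compare ETPB plus care-as-usual (CAU) or MB plus CAU with CAU". The first primary question there, repeated in the registration data set (Table 3), is: "Do participants receiving ETPB plus CAU or MB plus CAU have significantly lower anxiety, depression and outwardly directed irritability compared with those receiving CAU alone". The second has the same form for mother-infant interaction.

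The Statistical analysis section sets out the confirmatory tests. There are "Two analyses, performed in a hierarchical fashion so that no further" *p* value adjustment is considered necessary. First, "In analysis 1, the combined intervention groups (ETPB and MB) will be compared with CAU", at 2.5%. If that is significant, "analysis 2 will compare ETPB with MB as a primary analysis, to be judged at a 2.5% statistical significance level"; if not, Analysis 2 is still done but counts as secondary.

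The Power calculation section starts from the head-to-head comparison: "In order to have 90% power to detect an effect size of 0.4 for Analysis 2 (ETPB versus MB) 157 participants are required" in each intervention arm. It then adds 61 CAU participants for Analysis 1, giving 375 evaluable in a ratio of about 5:5:2, and 500 randomised after 25% attrition.

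Planned analysis names baseline-adjusted regression between intervention groups and lists no further contrasts. Economic Evaluation plans incremental costs and benefits of the treatment arms against CAU.

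**The concern.** The two programmes are not variants of one treatment. As the Interventions section describes them, ETPB rests on social learning theory and combines four antenatal groups with up to three home sessions and a final group. MB rests on attachment theory, with seven antenatal groups and one postnatal group. A significant pooled contrast shows that their average differs from CAU; it does not say which programme produced the difference.

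Attribution is left to Analysis 2, which asks a different question. Two programmes that work equally well should give a non-significant Analysis 2. In that favourable case the confirmatory plan ends with a positive pooled result and nothing about ETPB or MB by name, while the economic evaluation reports each arm against CAU with no matching confirmatory clinical contrast.

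**Working it through.** **Inputs.** From Statistical analysis: 2.5% per test, with the pooled test as gate. From Power calculation: effect size 0.4, 90% power, 157 per intervention arm, 61 CAU. Assumed: two-sided tests (this reproduces the 157), SD 1, no gain from baseline adjustment, no clustering by intervention group. Critical value 2.241; normal quantile for 90% power 1.282.

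**The plan's own figures.**
- Analysis 2: n per arm = 2(2.241 + 1.282)²/0.4² = 155.1, so 156 by the normal approximation and 157 by the t distribution. The stated 157 reproduces.
- Total: 375/0.75 = 500. Reproduces.
- Analysis 1: standard error √(1/314 + 1/61) = 0.1399; 0.4/0.1399 = 2.859; power Φ(2.859 − 2.241) = 73%. No separate effect size is given for Analysis 1; the stated 90% corresponds to about 0.49. That is a separate matter, but the 73% governs the gate below.

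**What the two analyses can establish.** Write e and m for the effects of ETPB and MB against CAU.
- Analysis 1 significant in favour of intervention and Analysis 2 significant: the average of e and m exceeds 0 and the better arm lies above that average, so the better arm exceeds CAU. The other arm's effect may be positive, zero or negative.
- Analysis 1 significant, Analysis 2 not: the average exceeds 0, and neither e nor m is established.

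**Error rate with two more contrasts.** The nulls are (e + m)/2 = 0, e = 0, m = 0 and e = m. Any two of them together force e = m = 0. So there are two cases:
- All four are true. Any false rejection needs the gate to open, which has probability 2.5%.
- At most one is true. It is tested at 2.5%, so the error is at most 2.5%.

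Simulation (1,000,000 replicates in each of 11 scenarios) gave 0.0249 with all nulls true and at most 0.0251 elsewhere. The simulation error is √(0.025 × 0.975/1,000,000) ≈ 0.0002.

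**Power of one programme against CAU.** Standard error √(1/157 + 1/61) = 0.1509; 0.4/0.1509 = 2.651; Φ(2.651 − 2.241) = 66% ungated (65% by the t distribution). Reaching 90% would need an effect of (2.241 + 1.282) × 0.1509 = 0.53, or about 154 CAU participants.

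**Behind the gate (same simulation).**

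| True effects (ETPB, MB) | Gate opens | ETPB v CAU | Both v CAU | ETPB v MB |
|---|---|---|---|---|
| 0.4, 0.4 | 73.1% | 63.4% | 54.7% | 1.8% |
| 0.5, 0.5 | 90.9% | 84.7% | 79.2% | 2.3% |
| 0.4, 0 | 20.9% | 20.8% | 1.3% | 18.9% |

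In the first row the present plan reaches a conclusion on a named programme in 1.8% of trials, by a chance difference between arms. In 73.1 − 1.8 = 71.3% it ends with the pooled result only. With the added contrasts, at least one programme is shown to differ from CAU in 72.1%.

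In the last row the pooled effect is 0.2: 0.2/0.1399 = 1.429 and Φ(1.429 − 2.241) = 21%. The gate is the bottleneck, and the added contrast gains about two percentage points over Analysis 2.

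**The case against.** Pooling first and then comparing head to head is a coherent design, and the sample size and 5:5:2 allocation were built on it. The primary questions join the programmes with 'or', which can be read as the pooled comparison; wording about either programme singly appears among the secondary questions. Nothing excludes arm-level contrasts as secondary analyses, and a SAP that is not shown may list them. All of this stands, and it is why the point is an improvement. It does not alter the fact that the protocol itself fixes which analyses are confirmatory, and that no single-programme comparison with CAU is among them.

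Three stronger readings are tempting and are not supported.
- A reader might infer that the trial cannot say which programme works. When both analyses are significant in favour of intervention, it can say so for the better arm.
- A reader might infer that an effect confined to one programme would go unseen. ETPB v MB has 90% power at 0.4 and is run even if Analysis 1 fails; what is lost, in about 79% of such trials, is its confirmatory status.
- A reader might set the 66% ungated power against the 21% gate and conclude that the extra contrasts rescue that case. As confirmatory tests they sit behind the same gate.

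**Conclusion.** The point holds as a gap in the confirmatory hierarchy, of moderate weight. Neither primary analysis tests ETPB or MB alone against CAU, and attribution is left open when Analysis 1 is significant and Analysis 2 is not. With both effects at 0.4, the chance of a confirmatory conclusion about a named programme rises from about 2% to 72% (63% for each, 55% for both). With only one effective programme it barely changes, from 19% to 21%. The added tests cost nothing in error rate, but the 61-participant CAU arm limits what they can show.

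The error-rate result is for one outcome and depends on there being three arms. The power figures rest on SD 1, two-sided 2.5% tests, no covariate gain and no clustering. A baseline correlation r multiplies the variance by 1 − r². With r = 0.5, which is an assumption and not in the protocol, the ungated 66% becomes Φ(0.4/(0.1509 × √0.75) − 2.241) = 79%. Clustering within intervention groups would work the other way.

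**What to change.** Amend the hierarchy in the protocol or SAP, before any comparison by arm is seen:
1. Keep Analysis 1 unchanged as the gate.
2. If it is significant, test ETPB v CAU, MB v CAU and ETPB v MB from the same baseline-adjusted model, each at 2.5% with no further adjustment, and give the short argument for why this holds with three arms.
3. Report both contrasts with CAU, with confidence intervals, whatever the gate shows, labelled secondary if Analysis 1 is not significant.
4. State the power limits: about 66% ungated at 0.4; behind the gate 63% each and 55% for both if both programmes work, and about 21% if only one does.

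The cost is a few sentences and two contrasts from a model already planned. No alpha and no participants are needed. Recruitment is reported as complete, so the CAU arm cannot be enlarged and the power limits must be stated as they are.

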#### Power calculation

In order to have 90% power to detect an effect size of 0.4 for Analysis 2 (ETPB versus MB) 157 participants are required in both the ETPB plus CAU and MB plus CAU groups. Comparing these 314 participants with CAU alone in analysis 1 (ETPB and MB vs CAU), requires 61 participants in the CAU alone group to achieve 90% power. Therefore, 375 participants are required in a ratio of ETPB:MB:CAU of approximately 5:5:2. To allow for 25% attrition at follow up, 500 participants will be recruited and randomised.

#### Planned analysis

Baseline-adjusted linear regression analysis (analysis of covariance) will be used to compare primary statistical outcomes between intervention groups. Similar methods will be used for other outcomes (using data transformation and alternative regression methods, depending on the distribution of each outcome). Regression models will be extended to investigate the effects of baseline characteristics and the potential moderating effects of these variables and other measures of intervention compliance. Repeated measures methods will be applied to outcomes collected at more than one post-baseline assessment.

For participants discontinuing from the study before the postnatal follow-up data collection, baseline data will continue to be analysed when consent is provided. Missing values will not be imputed. The sensitivity of the primary outcome analysis to missing values will be explored using multiple imputation, generating 10 imputed data sets, using all available data to predict missing values. Analyses will be conducted for the intention-to-treat population, consisting of all participants who have been randomised to the trial. In addition, analyses will also be undertaken for the per-protocol/on-treatment population.

For the economic analysis the incremental costs and benefits in each treatment arm will be reported within an incremental cost-effectiveness ratio (ICER) if appropriate. Within-trial analysis of costs and effects will be undertaken in STATA (StataCorp, TX, USA), adhering to good practice for economic evaluations alongside clinical trials [58, 59]. Missing data will be explored by employing multiple imputation methods using alternative configurations of baseline covariates [53, 60]. Based on the availability of linked routine data, longer-term costs and outcomes will be assessed by linking short-term outcomes identified in the study to potential longer-term impacts on health and wellbeing for both mother and infant, via trial extrapolation methods including economic modelling techniques.

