#### Baseline: 12–24 weeks pregnant

The baseline questionnaire (Additional file 2) will include the following validated measures:
The Brief Symptom Inventory (BSI-53; Question (Q)48 (Additional file 2)), which is a 53-item questionnaire covering nine symptom dimensions: somatization, obsession-compulsion, interpersonal sensitivity, depression, anxiety, hostility, phobic anxiety, paranoid ideation and psychoticism [31, 32]. The Global Severity Index from this scale will be used in randomisation to indicate severity of symptoms.The Hospital Anxiety and Depression Scale (HADS), which is a 14-item questionnaire assessing symptoms of anxiety and depression [33]. This will be enhanced by the 4-item outwardly directed irritability (I) questions adopted from the Adult Wellbeing Scale (AWS) [34], as a baseline measure for the primary outcome of maternal mental wellbeing (Q47).The EuroQol 5 Dimensions (EQ-5D-3 L; Q49), which is a standardized instrument to measure health-related quality of life, which will be used for health economic analyses [35].The 23-item Recent Life Events questionnaire (Q45), to determine the experience of specific events in the past year, and whether these affect the respondent [36, 37].The 12-item attitudes and pregnancy to the baby subscale from the Maternal Attitudes and Maternal Adjustment questionnaire (Q32) [38].The 28-item Childhood Trauma Questionnaire (Q89) as a measure of childhood abuse and neglect [39].

The baseline questionnaire will also include questions assessing reasons for vulnerability in pregnancy; socio-demographic characteristics including age, Scottish Index of Multiple Deprivation, ethnicity, education and employment; previous childbirth history and parity; health in pregnancy; and substance abuse [40].

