#### Follow up at 6 months postnatal (primary outcome end point)

The primary outcome of maternal mental wellbeing will be assessed by the HADS+I, included in the follow-up questionnaire (Additional file 3; Q35). The primary outcome of mother-infant interaction quality (MIIQ) will be measured based on the CARE Index Dyadic Synchrony Score [41] determined from an episode of play recorded during the follow-up visit when the infant is around 6 months old.

In addition to the HADS+I, the follow-up questionnaire will include the following listed validated measures that will be analysed as secondary outcome measures:

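### The baseline-adjusted ANCOVA has no outcome baseline to adjust for in mother-infant interaction quality, and the stated model does not name the three stratification factors

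*Protocol article*

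**What the plan says.** The *Planned analysis* section gives one method for the primary outcomes, in the plural: "Baseline-adjusted linear regression analysis (analysis of covariance) will be used to compare primary statistical outcomes". It lists no covariates. The only other mention of baseline variables there is that "Regression models will be extended to investigate the effects of baseline characteristics and the potential moderating effects of these variables", which describes further models.

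There are two primary outcomes. HADS+I is collected at baseline expressly "as a baseline measure for the primary outcome of maternal mental wellbeing (Q47"). MIIQ, the CARE Index Dyadic Synchrony Score, is "determined from an episode of play recorded during the follow-up visit when the infant is around 6 months old". The baseline section is headed "Baseline: 12–24 weeks pregnant" and names no counterpart for MIIQ.

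The *Randomisation* section states that allocation is "stratified by parity (number of children), severity of psychiatric symptoms (measured by the BSI, 53) and history of substance dependency", in the ratio "For every 12 participants randomised, two will receive CAU, five will be offered ETPB and five will be offered MB".

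**The concern.** The usual meaning of a baseline-adjusted ANCOVA is a regression of the outcome on treatment and on the same measure taken before randomisation. HADS+I allows this. MIIQ does not, because there is no infant to interact with at baseline. Followed in that sense, the sentence reduces to an unadjusted comparison for one primary outcome.

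The second element concerns stratification. Balancing the arms on prognostic factors removes between-stratum variation from the treatment difference. A model without those factors still counts that variation as residual error, so its standard error is larger than the true sampling error. Intervals come out too wide and tests too strict.

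At stake is power for MIIQ in analysis 1 (both interventions against care as usual), which decides whether analysis 2 counts as primary. The trial was sized on maternal mental wellbeing alone, so MIIQ has no power calculation of its own. An adjustment left undefined for a primary outcome also leaves room to choose covariates after the data are seen.

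**Working it through.** **Inputs from the protocol article.** 157 completers in each intervention arm, 61 in care as usual, 375 in total; effect size 0.4 SD (stated for analysis 2); significance level 2.5% per analysis; 25% attrition; allocation 5:5:2.

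**Assumptions.** Two-sided tests (the article does not say, but two-sided reproduces its sample size). An effect of 0.4 SD for MIIQ in analysis 1. The stratification factors explain a share R² of MIIQ variance; the article gives no value, so 0.05, 0.10 and 0.20 are shown.

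**Step 1. Reproduce the plan's figures.** For two means at 0.4 SD, two-sided 2.5% and 90% power, the normal formula gives 156 per arm and the noncentral t gives 157 (power 90.1%). 157 + 157 + 61 = 375, and 375 / 0.75 = 500. These agree with the article.

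**Step 2. Analysis 1 before any adjustment.** Effective size is 314 × 61 / 375 = 51.08. The noncentrality is 0.4 × √51.08 = 2.859 and the critical value is 2.2414. Power is Φ(2.859 − 2.2414) = Φ(0.617), or 73%.

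**Step 3. Effect of omitting the factors.** With stratified allocation, the true standard error of the estimate is about √(1−R²) times the one that the unadjusted model reports. Hence:

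- excess interval width: 1/√(1−R²) − 1
- true size of the unadjusted test: 2 × [1 − Φ(2.2414/√(1−R²))]
- power without the factors: Φ(0.617/√(1−R²))
- power with the factors: Φ(2.859/√(1−R²) − 2.2414)

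| Assumed R² | Interval too wide by | True size at nominal 2.5% | Power without factors | Power with factors |
|---|---|---|---|---|
| 0.05 | 2.6% | 2.15% | 74% | 76% |
| 0.10 | 5.4% | 1.8% | 74% | 78% |
| 0.20 | 11.8% | 1.2% | 75% | 83% |

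**Step 4. Simulation check.** Stratified blocks of 12 in 5:5:2, 375 participants, 8 strata, 4,000 runs per setting. Analysis 1 power without and with the factors was 75% and 77% (R² 0.05), 75% and 78% (0.10), and 76% and 83% (0.20). Rejection under no effect, without the factors, was 2.0%, 1.9% and 1.3%.

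**Step 5. Where the error sits.** In the simulation at R² = 0.20 with no effect, the standard deviation of the estimate was 0.127 without the factors and 0.126 with them. The mean reported standard error was 0.139 and 0.124. Stratification already protects the estimate; the model without the factors misreports its uncertainty.

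**Step 6. Equivalent sample size.** Let k multiply the sample so that the unadjusted test reaches the adjusted power: (2.859√k − 2.2414)/√(1−R²) = 2.859/√(1−R²) − 2.2414. This gives k of about 1.08 at R² = 0.10 and 1.17 at R² = 0.20, that is, 8% and 17% more participants.

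**Step 7. HADS+I.** This model already has its own baseline. Assume correlations of 0.5 to 0.6 between baseline and outcome, 0.7 to 0.8 between BSI and baseline HADS+I, and 0.4 to 0.5 between BSI and outcome. Omitting BSI then makes the interval only about 0 to 3% wider.

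**The case against.** The strongest reply is that the article is silent rather than wrong. It lists no covariates, and a covariate list is commonly left to the full protocol or the analysis plan, neither of which is shown. A regression of MIIQ on other baseline variables is also a baseline-adjusted ANCOVA, so the sentence can be read to cover it.

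Much of this stands. A reader might infer that the MIIQ analysis cannot be carried out, or that the trial has decided to leave the stratification factors out. The text supports neither: adjustment for other covariates is feasible, and the factors are neither included nor excluded. A reader might also infer that the treatment estimate itself loses precision, that false positives rise, or that the loss equals 1/(1−R²) − 1 in participants (11% at R² = 0.10, 25% at 0.20). Steps 3, 5 and 6 show otherwise.

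R² is assumed, and at 0.05 the power loss is only about 2 points. The 0.4 SD effect is borrowed from the outcome used to size the trial.

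What the reply does not remove is that one sentence fixes a method for two primary outcomes and, on its natural reading, fits only one of them. That goes beyond an unlisted detail.

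**Conclusion.** The point holds as a free improvement. MIIQ has no baseline value, the article does not say what its adjustment means for that outcome, and the stated primary model does not name the stratification factors. If the adjustment is taken as the outcome's own baseline, MIIQ is compared without adjustment and its reported standard error is too large. For assumed R² of 0.05, 0.10 and 0.20, intervals are about 3%, 5% and 12% too wide, and true size is about 2.2%, 1.8% and 1.2% against a nominal 2.5%. Analysis 1 loses about 2, 3 to 4, and 7 to 8 points of power at an assumed 0.4 SD.

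The direction is conservative, so no false claim of benefit follows. For HADS+I, the outcome on which the trial was sized, little changes.

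**What to change.** State that both primary models include parity, BSI severity and history of substance dependency. Add baseline HADS+I to the HADS+I model. State that for MIIQ, adjustment for baseline means adjustment for these three factors.

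Further MIIQ covariates, such as maternal age or the Childhood Trauma Questionnaire score, are optional; the article offers no evidence that they predict the Dyadic Synchrony Score. If they are wanted, they should be fixed before the data are seen.

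The cost is a sentence or two of wording in the analysis section. The three factors and HADS+I are already determined from the baseline questionnaire, so no new data or participants are needed.
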